## Abstract

**Background:**

Ischemic cardiomyopathy and severe left ventricular dysfunction are well established to represent the main determinants of poor survival and premature death compared with preserved ventricular function. However, the role of myocardial revascularization as a therapeutic alternative is not known to improve the long-term prognosis in this group of patients. This study will investigate whether myocardial revascularization contributes to a better prognosis for patients compared with those treated with drugs alone and followed over the long term.

**Methods:**

The study will include 600 patients with coronary artery disease associated with ischemic cardiomyopathy. The surgical or drug therapy option will be randomized, and the events considered for analysis will be all-cause mortality, nonfatal infarction, unstable angina requiring additional revascularization, and stroke. The events will be analyzed according to the intent-to-treat principle. Patients with multivessel coronary disease and left ventricular ejection fraction measurements of less than 35% will be included. In addition, myocardial ischemia will be documented by myocardial scintigraphy. Markers of myocardial necrosis will be checked at admission and after the procedure.

**Discussion:**

The role of myocardial revascularization (CABG) in the treatment of patients with coronary artery disease and heart failure is not clearly established. The surgical option of revascularizing the myocardium is a procedure designed to reduce the load of myocardial hibernation in patients with heart failure caused by coronary artery disease. On the other hand, the assessment of myocardial viability is frequently used to identify patients with left ventricular ischemic dysfunction in which CABG may add survival benefit. However, the effectiveness of this option is uncertain. The great difficulty in establishing the efficacy of surgical intervention is based on the understanding of viability without ischemia. Thus, this study will include only patients with viable and truly ischemic myocardium to correct this anomaly.

**Trial registration:**

Evaluation of a randomized comparison between patients with coronary artery disease associated with ischemic cardiomyopathy submitted to medical or surgical treatment: MASS-VI (HF), ISRCTN77449548, Oct 10th, 2019 (retrospectively registered).

## Background

The Coronary Artery Surgery Study (CASS) was the pioneer in randomly identifying those patients with stable coronary artery disease (CAD) and preserved ventricular function who have a favorable prognosis. In addition, it reported that clinical and surgical treatments had a similar mortality occurrence in long-term follow-up [1]. Subsequent studies, such as the Veterans Administration Cooperative Study Group (VA) [2] and the European Coronary Surgery Study Group (European) [3], have found similarities in results relative to clinical or surgical treatments. However, unlike the CASS study, these studies included non-similar patients with unstable angina (European) and compromised ventricular function including ventricular aneurysms in the study sample. In addition, they observed increased incidences of death and nonfatal infarction in certain subgroups of patients [4]. These differences were attributed to the selection of patients with different degrees of clinical presentation and arterial and ventricular impairment. In fact, CASS, through a sub-analysis, identified that patients with ventricular dysfunction in clinical treatment evolved with increased mortality compared with those with preserved ventricular function undergoing myocardial revascularization [5].

Similarly, the Bypass Angioplasty Revascularization Investigation (BARI), which studied patients with preserved ventricular function, found a worse prognosis in patients with diabetes mellitus who underwent percutaneous treatment [6]. On the other hand, subsequent studies in diabetic patients and preserved ventricular function found no differences in mortality compared with the different therapeutic forms of CAD [7, 8]. In this scenario, the Stich Trial [9] was designed to compare only patients with multi-arterial CAD and ventricular dysfunction in different therapeutic forms. In our study, we did not find significant survival-related differences between clinical treatments and surgical revascularization, thus adding doubts to the understanding of the prognosis of the interventional treatment of ventricular dysfunction. Notably, the Stich Trial included patients with ventricular dysfunction but without the presence or absence of myocardial ischemia being identified.

This purpose of this study was to evaluate, in a randomized model, the results of surgical or medical treatments in patients with coronary artery disease and left ventricular dysfunction secondary to ischemic cardiomyopathy.

This is a prospective randomized clinical trial, with a 1:1 allocation ratio, designed to test the superiority of coronary artery bypass surgery over medical therapy alone in patients with coronary artery disease and left ventricular dysfunction secondary to ischemic cardiomyopathy.

## Methods/Design

A total of 600 patients with angina pectoris will be screened for conventional coronary artery disease with obstructive lesions ≥ 70% of the arterial lumen and left ventricular dysfunction; 300 patients will be randomized to myocardial revascularization surgery, and another 300 patients will receive drug treatment. Patients who have been victims of acute myocardial infarction (AMI) in the previous 6 months, are on dialysis, or have disabling degenerative disease will not be included. In addition, patients who refuse to sign a consent form or who do not accept a possible surgical randomization will not be included. The stages of randomization are described in Fig. 1 (Patient selection flowchart). This is a study performed at an Academic Hospital. All data for inclusion, follow-up, and occurrence of events will be collected in a single center in Brazil.

**Fig. 1 Fig1:**
[figure not shown]
Patient selection flowchart

### Surgical treatment

Patients randomized to surgery should have ventricular dysfunction with ejection fraction ≤ 35% and have lesions in multiple arteries. Surgery should be performed with the aid of extracorporeal circulation in all patients. In this procedure, the myocardial protection should be made with a standardized cardioplegic solution with a temperature close to 35 °C. Native vessels may receive venous grafts or arterial anastomoses at the discretion of the surgeon. Chronically occluded arteries may receive associated arterial or venous grafts. Obstructed artery endarterectomy may be the surgeon’s option. In addition to surgical intervention, patients will receive full medication for CAD as well as rigorous control of risk factors.

### Medical treatment

Both trial arms will be placed into optimal medical therapy that will include maximum tolerated beta-blockers, angiotensin-converting enzyme inhibitors or angiotensin receptor blockers, spironolactone, and diuretics if necessary. Antiplatelets agents, statins, and lifestyle changes will also be prescribed in each study visit.

Patients randomized to drug therapy will undergo laboratory tests on admission that include markers of myocardial necrosis, renal function tests, and liver tests for the detection of lipid or glycemic disorders. All patients will receive specific medications to control anginal symptoms as well as associated illnesses. Lifestyle changes and strict control of risk factors will be emphasized. Multiprofessional teams will be available to control this condition.

### Laboratory tests

Patients undergoing surgery will have routine biochemical exams before and after surgery. In addition, C-reactive ultra-sensitive protein (CRP) will be checked immediately before and after surgery. In addition, biomarkers of myocardial necrosis will also be checked before and after the surgical procedure. Electrocardiography will be performed before and after the operation, and echocardiography will be performed before and after the operation for analysis of ventricular function.

### Myocardial scintigraphy

At study admission all patients will undergo scintigraphic examination for the detection of ischemic areas. The quality of the images and also the ischemic area under risk will be considered for analysis. For inclusion in the study, ≥ 10% of the area at risk will be considered.

### Echocardiography

Patients in the surgical group will undergo echocardiography immediately before the procedure, at hospital discharge, and 1 year after the procedure. Simpson’s biplanar method will be employed. In patients in the clinical group, echocardiography will be performed at admission, after 1 year, and at the end of follow-up.

### Primary endpoint of the study

Combined primary endpoints will be considered as those that occurred during the study: death from any cause, nonfatal myocardial infarction, stroke and unstable angina requiring additional intervention.

The definitions of each event are available in Table 1.

**Table 1 Tab1:** Definitions of combined endpoints

**Mortality from any cause**	Mortality from any cause is included as a composite primary event. Cardiovascular death includes that from myocardial infarction, sudden death, refractory heart failure, fatal hemorrhagic cerebral infarction or fatal cerebral hemorrhage related to the procedure.
**Vascular brain accident**	Patients with focal neurological deficit of central origin lasting more than 72 h or a focal neurological deficit of central origin that lasted more than 24 h, with evidence of images of cerebral infarction or intracerebral hemorrhage, or non-focal encephalopathy that lasted more than 24 h, with evidence of images of cerebral infarction or bleeding sufficient to warrant clinical status. Retinal arterial ischemia or bleeding is also included. To meet the definitions of stroke, the deficit must be new or sudden—consensually—not attributable to any alternative.
**Acute myocardial infarction**	Elevation of specific cardiac enzymes within 14 days of the revascularization procedure and the presence of new Q waves in at least two or more contiguous ECG leads, and elevation of 10x the 99th percentile of CK-MB and ultrasensitive troponin.
**Additional revascularization**	Initial revascularization is considered complete when the patient is transferred from the operating room to the ward. Refractory angina requiring additional revascularization is considered an event.

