### Secondary endpoint

The secondary endpoint, during the study follow-up, will be the graduation of anginal symptoms and also of heart failure. Cardiac decompensation hospitalization will be considered a secondary event

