### Statistical analysis

Patients eligible for the MASS-VI (HF) study will be invited to attend the Heart Institute– FMUSP outpatient clinic to receive additional information. Candidates for surgical treatment when admitted will be visited by one of the study doctors. After giving consent, patients will be randomized. To ensure a reasonable balance of the sample, the assignment is made according to a computer-generated list of randomly permuted blocks that are unknown to the investigators. The generation of the allocation sequence is in the statistics department without the possibility of access to researchers.

After randomization, patients will be scheduled for the intended treatment. The design is open label with only outcome assessors being blinded, so unblinding will not occur. The objective of the main analysis is to compare the results of the primary events of this study. Kaplan-Meier curves will be used for graphical comparison of the data. All values will be expressed as mean ± standard deviation or percentage. The continuous variables will be compared by the Wilcoxon test, whereas the variables will be analyzed with the Fisher exact test. The occurrence of event results will be compared using the Cox proportional hazards model, reflecting a risk rate. The analysis of the primary objectives will be based on the intention-to-treat principle. Interim analyses will be conducted annually to assess safety. For both treatment strategies, the cost of diagnostic procedures, treatment procedures, complications, and short- and long-term effect differences will be estimated. Marginal costs in monetary terms will be calculated by multiplying unit costs and marginal medical consumption as recorded for each patient.

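### Death counts only inside a composite with an open-label revascularization component, so a positive primary result need not mean any difference in death, infarction or stroke

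*Protocol article*

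**What the plan says.** The Abstract (Background) of the protocol article says that "the role of myocardial revascularization as a therapeutic alternative is not known to improve the long-term prognosis in this group of patients", and asks "whether myocardial revascularization contributes to a better prognosis for patients compared with those treated with drugs alone and followed over the long term". The Abstract (Discussion) refers to the use of viability testing to "identify patients with left ventricular ischemic dysfunction in which CABG may add survival benefit" and calls the effectiveness of surgery uncertain. The Background section cites an earlier trial without significant survival differences as the reason for doubt. It then describes the present trial as "designed to test the superiority of coronary artery bypass surgery over medical therapy alone".

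The section Primary endpoint of the study defines one composite: "death from any cause, nonfatal myocardial infarction, stroke and unstable angina requiring additional intervention". Table 1 there words the last component as refractory, not unstable, angina leading to additional revascularization. It ties infarction to marker elevation in the 14 days after a revascularization procedure.

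Under Secondary endpoint: "The secondary endpoint, during the study follow-up, will be the graduation of anginal symptoms and also of heart failure". Hospitalization for cardiac decompensation is added. The ancillary outcomes are SF-36 quality of life and cost-effectiveness. Neither death alone nor death, infarction or stroke is listed.

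Under Statistical analysis: "The design is open label with only outcome assessors being blinded". The primary comparison uses Kaplan-Meier curves and a Cox model, by intention to treat.

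**The concern.** The first three components are outcomes on which the article calls the benefit of surgery uncertain. The fourth differs in two ways.

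- It needs a decision to intervene, taken by treating clinicians who know the arm. Blinded assessors can check that an event meets the definition, but they cannot undo the unblinded decision that produced it.
- Every patient enters with angina and at least 10% of myocardium at risk, and only one arm is revascularized at the start. The Discussion section treats symptom relief from grafts as intuitive. A difference in this component is therefore expected whatever happens to death, infarction or stroke.

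No listed secondary endpoint would show whether a positive composite reflects fewer deaths, infarctions or strokes, or only less later revascularization. The risk is that a difference of the second kind is reported as the better prognosis the trial was set up to examine.

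**Working it through.** **The plan's own figure.** Sample size calculation gives 585 patients, alpha 5%, beta 20% and 9% in the medical arm. It states no surgical-arm rate, hazard ratio, time base for the 9% or component split, so 585 can be neither reproduced nor refuted. If 9% is cumulative and the test is a two-sided comparison of two proportions, a surgical-arm rate of about 3.4% gives 290 per arm (580 in total), a relative reduction of (9 − 3.4)/9 = 62%.

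**Inputs for the check.** From the article: 300 per arm, 9% in the medical arm, a visit schedule to 60 months and alpha 5% (taken as two-sided). Assumed, because the article gives nothing: the share of the fourth component, the effect of surgery on it, and no effect on death, infarction or stroke. First procedures in the medical arm are assumed to count as events.

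**Reading A: 9% per year for 5 years (an assumption), fourth component cut by 80%.**

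Medical-arm cumulative hazard: H0 = −5 ln(0.91) = 0.472, so p0 = 1 − exp(−0.472) = 0.376. If the component is a share s of that hazard, HR = 1 − 0.8s and p1 = 1 − exp(−0.472 × HR). Expected events are d = 300(p0 + p1). The chance of significance is Φ(|ln HR| × √d / 2 − 1.96).

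| Share s | HR | p1 | Events | Chance of significance |
|---|---|---|---|---|
| 10% | 0.92 | 0.352 | 218 | 9% |
| 20% | 0.84 | 0.327 | 211 | 24% |
| 30% | 0.76 | 0.301 | 203 | 50% |
| 40% | 0.68 | 0.274 | 195 | 77% |
| 50% | 0.60 | 0.246 | 187 | 94% |

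For s = 40%: |ln 0.68| = 0.386, √195.1 / 2 = 6.98, product 2.69, and Φ(2.69 − 1.96) = 0.77.

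**Reading B: 9% cumulative, no fourth-component events after surgery.**

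With pM = 0.09 and pS = 0.09 minus the component, the chance is Φ((pM − pS − 1.96 × SE0)/SE1). Here SE0 uses the pooled rate and SE1 the separate rates.

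| Component, of the 9 points | Surgical-arm composite | Chance of significance |
|---|---|---|
| 3 | 6% | 29% |
| 4 | 5% | 48% |
| 5 | 4% | 70% |
| 6 | 3% | 87% |
| 7 | 2% | 97% |

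For 5 points: SE0 = √(0.065 × 0.935 × 2/300) = 0.0201, SE1 = √((0.09 × 0.91 + 0.04 × 0.96)/300) = 0.0200, and Φ((0.05 − 0.0395)/0.0200) = 0.70.

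**Where death, infarction and stroke dominate.** With these events equal at 40% in both arms, and the fourth component at 10% against 2% (independent), the composite is 46.0% against 41.2% and the chance is 22%. With these events at 20% and the component at 15% against 3%, it is 32.0% against 22.4% and 75%.

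**The offset.** Infarction as defined in Table 1 follows a procedure, so it falls mainly on the operated arm. In Reading B with 5 points, one extra percentage point in the surgical arm makes the comparison 9% against 5%, and the chance drops from 70% to 48%. Two extra points (9% against 6%) give 29%.

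**The case against.** - **The article is condensed.** Component results are often left to a full protocol or analysis plan. The article also writes of primary endpoints and events in the plural, so component analysis may be intended. That stands: a reader might infer that no component analysis will be done, and the article does not show that. But the endpoint list is stated, in sections of its own, and gives death no rank outside the composite.
- **Survival is not the formal objective.** A reader might infer that the endpoint contradicts the trial's question. The stated purpose is broader, namely the results of the two treatments, and prognosis is nowhere confined to death, infarction and stroke. Survival is the motivation, so this is a mismatch of emphasis and not a contradiction.
- **The fourth component is not elective crossover.** It requires unstable or refractory angina. That stands, so it goes too far to say that a positive result could only mean operations done later. The decision to intervene is still made unblinded.
- **The direction may not favour surgery.** The infarction definition counts against surgery. If *additional* excluded a first procedure in the medical arm, the fourth component would arise almost only after surgery. This weakens any claim of a known bias towards surgery, but not the point that the component is not comparable between arms.

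**Conclusion.** The point holds as a design weakness. As the endpoints are listed, a significant composite could arise with no difference in death, infarction or stroke, and no named endpoint would show it.

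The size cannot be fixed from the article. Across the assumptions shown, the chance runs from about 9% to 94% with 9% read as annual and from 29% to 97% with 9% read as cumulative. Any early procedure-related infarction excess in the surgical arm would lower these figures. It would be tempting to quote a single figure such as 77%, but that rests on an undocumented annual rate and one chosen component share. These numbers show that the outcome is possible, not that it is likely.

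**What to change.** 1. First reconcile two definitions so that they apply equally to both arms. In Table 1 the infarction definition is limited to the 14 days after a procedure. The fourth component is called unstable angina in the endpoint text and refractory angina in Table 1, and it should be clear whether a first procedure in the medical arm counts as *additional*.
2. Keep the composite as primary. Under Secondary endpoint, name all-cause death, then time to first death, nonfatal infarction or stroke, as the first-ranked secondary endpoints. Analyse them by intention to treat with the same Cox model, and report hazard ratios and confidence intervals beside the composite and each of its components.
3. State that a positive composite alone will be described as a reduction in the composite, and not as improved survival.

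Cost: wording only. The schedule already records events at every visit, and three patients had been enrolled at first submission. The downsides are a narrower claim from a positive primary result and limited power for the new secondary endpoints, which should be read through their confidence intervals.

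### Table 1 defines myocardial infarction only as a procedure-related event, so non-procedural, nonfatal infarctions that the primary endpoint is meant to count cannot qualify in either arm

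*Protocol article*

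**What the plan says.** The section Primary endpoint of the study (protocol article) lists the composite as "death from any cause, nonfatal myocardial infarction, stroke and unstable angina requiring additional intervention". It sets the period with "Combined primary endpoints will be considered as those that occurred during the study", and the visit schedule under Ambulatory follow-up runs to 60 months. It then refers the reader on: "The definitions of each event are available in Table 1".

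Table 1 has one row for acute myocardial infarction. It opens with "Elevation of specific cardiac enzymes within 14 days of the revascularization procedure and the presence of new Q waves" in at least two contiguous leads, and ends with "and elevation of 10x the 99th percentile of CK-MB and ultrasensitive troponin". The criteria are joined by 'and'. There is no alternative branch and no second row. Elsewhere the article names infarction as an event (Abstract) or as an exclusion when recent (Methods/Design), but does not define it.

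The Background states that the trial tests superiority of surgery over medical therapy alone. Statistical analysis specifies intention to treat and a Cox model.

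**The concern.** The 14-day window is anchored to a revascularization procedure. Half of the patients are randomized to a strategy that has none. Read literally, the row makes the component unreachable for a medical-arm patient who is never revascularized, and for a surgical patient once the window has closed, unless a further procedure reopens it.

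Two consequences follow for a superiority comparison. Procedural infarctions count, and they fall almost wholly in the surgical arm, so this component is tilted against surgery. Later nonfatal infarctions, which surgery is hoped to prevent, count for neither arm, so any benefit on them is invisible to the composite. The row also conflicts with the statement in the same section that events during the whole study count.

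**Working it through.** **1. Who can meet the infarction row as written**

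| Event | Infarction row met? | Counted in the composite by another route? |
|---|---|---|
| Nonfatal infarction within 14 days of surgery, with new Q waves and the tenfold rise | Yes | Not needed |
| Nonfatal infarction after day 14, surgical arm, no further procedure | No | Only if it leads to additional revascularization for unstable or refractory angina |
| Nonfatal infarction, medical arm, never revascularized | No | No |
| Nonfatal infarction, medical arm, within 14 days of a crossover procedure | Possible | Not needed |
| Fatal infarction, either arm, any time | Not needed | Yes, as death from any cause |

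What is lost is the nonfatal, non-procedural infarction that is not followed by death or additional revascularization. This result needs no arithmetic.

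**2. The plan's own sample size**

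Inputs from Sample size calculation: 9% in the medical arm, alpha 5%, beta 20%, 585 patients. The surgical-arm rate, sidedness and time horizon are not given, so 585 cannot be derived; only the implied effect can be back-solved.

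- Two proportions, two-sided, no continuity correction, 585/2 = 292.5 per arm, 80% power: implied surgical rate 3.42%. (At 3.4% the formula gives N = 580.)
- Two proportions, one-sided: 3.9-4.0% gives N = 572-600.
- If 9% were annual over 5 years: a hazard ratio of 0.66 needs 188 events and N = 585 (Freedman, two-sided).

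These readings differ widely, so any power statement depends on the one chosen.

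**3. Illustration of the possible loss of power**

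Assumptions: true rates 9% v 3.42%, n = 300 per arm, two-sided 5%, and a share s of events that are uncounted infarctions. The documents do not give s; 20-40% is assumed.

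Power = Φ{ [ |p1 − p2|·√n − 1.96·√(2·p̄·(1 − p̄)) ] / √(p1(1 − p1) + p2(1 − p2)) }, with p̄ = (p1 + p2)/2.

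Starting point: p1 − p2 = 0.0558, and times √300 this is 0.966. p̄ = 0.0621, so 1.96·√(2 × 0.0621 × 0.9379) = 0.669. The denominator is √(0.0819 + 0.0330) = 0.339. Power = Φ(0.878) = 81%.

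| s | Both arms lose share s | Power | Medical arm only loses share s | Power |
|---|---|---|---|---|
| 0 | 9.0% v 3.42% | 81% | 9.0% v 3.42% | 81% |
| 20% | 7.2% v 2.74% | 71% | 7.2% v 3.42% | 54% |
| 30% | 6.3% v 2.39% | 65% | 6.3% v 3.42% | 37% |
| 40% | 5.4% v 2.05% | 58% | 5.4% v 3.42% | 22% |

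The right-hand case is the extreme one: it supposes that surgical patients lose no infarctions, although those after day 14 are uncounted too.

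**The case against.** **The article condenses a fuller protocol.** A spontaneous-infarction rule may stand there. The row also mentions enzyme elevation twice, which suggests garbled wording rather than a deliberate choice. This limits what can be said about the trial's conduct. It does not excuse the text, which prints a definition and says that the table defines each event. If a fuller document says otherwise, the two must be reconciled.

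**A reader might infer that every spontaneous infarction goes uncounted.** The documents do not support that. Fatal infarctions count as deaths, and those leading to additional revascularization count under that component.

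**A reader might infer a definite loss of power, or a definite number of extra surgical events.** Neither follows. The infarction share has no source in the article and the 3.42% is back-solved. A guess of 2-5% procedural infarctions would mean 6-15 in 300 surgical patients, but 3.42% of 300 is only about 10 primary events of all kinds. The upper guess contradicts the rate it would be set beside.

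**A reader might infer unequal ascertainment.** For surgery, "biomarkers of myocardial necrosis will also be checked before and after the surgical procedure", while "Patients randomized to drug therapy will undergo laboratory tests on admission that include markers of myocardial necrosis". But the visit schedule does not differ by arm. It has ECGs at 1, 12, 24, 36, 48 and 60 months and laboratory tests, including CK-MB and troponin, yearly from 12 months. Yearly sampling would not catch an acute infarction, but ECGs could show new Q waves in either arm. The difference around surgery exists because only one arm has a planned procedure.

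**A reader might infer that the row defeats blinding.** The article says "The design is open label with only outcome assessors being blinded". Applying the row does require knowing that a procedure took place, but so does the additional-revascularization row, and so would any procedure-related rule in a corrected table. This is not a separate defect that the fix would cure.

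**Conclusion.** The point stands on the text. Table 1 gives infarction a procedure-related definition only, in conflict with the section's own statement that infarction counts throughout the study. Followed as written, the component can arise almost only in revascularized patients. It is therefore biased against surgery, and infarctions that surgery might prevent are omitted. Because this is a primary-endpoint component in a superiority trial, it should be corrected before the composite is analysed.

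The size cannot be derived from the document. The illustrated fall from 81% to 71-58% (equal loss) or to 54-22% (medical arm only) rests on the assumed 20-40% share, the back-solved surgical rate and a two-sided test of proportions. It shows that the definition could matter materially. It is not an estimate for this trial, and the conclusion does not depend on it.

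**What to change.** - Label the existing row procedure-related infarction and state that it applies to any revascularization: index, crossover or repeat.
- Add a definition of non-procedural (spontaneous) infarction, applied identically to both arms from randomization to the end of follow-up.
- State that both kinds count in the primary composite.
- Pre-specify a sensitivity analysis of the composite without procedure-related infarction, so that the effect of early procedural events on the comparison is visible.

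The cost is a protocol amendment and a review of events already recorded under the existing row. Trial status reports three patients enrolled at submission of the article, with recruitment expected to run to mid-2024. How many events need review depends on when the change is made and cannot be told from the document. The visit schedule has a history/events entry at every visit, but the article does not say whether the detail needed to classify a spontaneous infarction is recorded there, so this should be checked.
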